### Additional analyses

Process and economic evaluations, including analyses of linked data, will be reported separately.

### Harms

#### Adverse events and serious adverse events

Safety will be defined by the number and frequency of reported adverse events and serious adverse events related to the intervention and will be reported using a format shown in Supplemental Table III. Such adverse events will include falls or accidents requiring medical attention or presentations to hospital. Moreover, deaths, disability/incapacity, or other life-threatening or important medical events related to the intervention will also be reported.

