### Randomisation and blinding

Randomisation is undertaken through the REDCap online system [7], with stratification balancing by age (< 65 or 65+ years) and level of disability (based on a baseline modified Rankin Scale [scores 0–2 for none-minor disability, 3–4 for moderate-severe disability]). The randomisation table, comprising the allocation sequence, block sizes, and stratification balancing, was developed outside of REDCap by an independent data analyst and imported into the REDCap study database.

The trial has a double-blind design. Therefore, hospital staff, participants, outcome assessors, and trial biostatisticians are unaware of group allocation. To ensure that blinding of participants to group allocation is maintained, the trial is described in the patient information and consent form in general terms as “providing post-hospital discharge support” [8]. Specifically, intervention approaches were broadly described in the patient information and consent form as including the “setting of specific recovery goals with trained clinicians, receiving electronic self-management information sent via SMS or email, and participation in follow-up assessments”. Outcome assessors also use an interview script to standardise outcome assessments undertaken by telephone interview and are trained to avoid entering into general discussions. To ensure hospital clinicians and participants are unaware of the allocation group, all eligible consenting patients complete goal setting, using the ReCAPS “goal setting menu”, and data collection at baseline is standardised. The trial biostatistician who will undertake the analysis is also blinded to group allocation.

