### Statistical interim analyses and stopping guidance

An independent Data Safety and Monitoring Committee (DSMC) was established to safeguard the interests of trial participants, by assessing the safety of the intervention during the trial, and the general progress of the trial. The committee comprises one neurologist, a senior academic physiotherapist who has expertise in digital health randomised clinical trials and a senior clinical trials biostatistician. Specifically, the role of the DSMC is as follows: (a) periodically monitor and review participant safety in the trial, (b) monitor effectiveness, and (c) review participant recruitment, accrual, retention, and withdrawal.

The DSMC met at least once per year until November 2020 and have met twice per year subsequently, with a total of seven meetings as of September 2023. The committee recommended the trial to continue based on the interim analysis of the primary outcome from the first 50 participants (~6% of the estimated sample size). All interim analyses are being undertaken by a data analyst who is blinded to the group allocation. The principal investigator has the responsibility to report data on any severe adverse events to the DSMC and the independent medical monitor, if needed. The medical monitor is a neurologist who reviews serious adverse events, if deemed to be related to the intervention, and adjudicates on unplanned/planned hospital readmissions. The DSMC is also tasked with formulating recommendations relating to the selection/recruitment/retention of participants, participant management, improving adherence to protocol-specified regimens, and the procedures for data management and quality control based on these interim analyses.

There are no strict stopping criteria, but the DSMC have a responsibility to provide recommendations about continuing, modifying, or stopping the trial, in line with the DSMC charter. Following an interim analysis, the trial may be stopped for safety reasons without rejecting any null hypotheses, i.e. there is no planned adjustment of the significance level due to interim analyses. 

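### The Harms section counts only events related to the intervention, which is a poor basis for comparing harms between arms; all reported events should be tabulated by arm, with relatedness as an added column

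*SAP article*

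**What the plan says.** The SAP article, Adverse events and serious adverse events, gives the rule: "Safety will be defined by the number and frequency of reported adverse events and serious adverse events related to the intervention". It then names event types: "Such adverse events will include falls or accidents requiring medical attention or presentations to hospital". The last sentence carries the qualifier over to the gravest events: "deaths, disability/incapacity, or other life-threatening or important medical events related to the intervention will also be reported". The layout is left to Supplemental Table III, which is not shown. The text describes no between-arm test of adverse events.

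Statistical interim analyses and stopping guidance has two statements on who sees what. The principal investigator is to "report data on any severe adverse events to the DSMC and the independent medical monitor, if needed". The medical monitor "reviews serious adverse events, if deemed to be related to the intervention, and adjudicates on unplanned/planned hospital readmissions". Neither section says who judges relatedness or by what criteria.

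Under Randomisation and blinding, "hospital staff, participants, outcome assessors, and trial biostatisticians are unaware of group allocation". The Introduction says that controls get at most seven administrative messages and no healthcare content. All consenting patients complete the baseline goal setting.

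**The concern.** In a randomised trial, comparing all events by arm shows whether the intervention causes harm. Case-by-case attribution adds clinical description but is weaker evidence, for two reasons that apply here.

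- **The arms differ in what an event could be related to.** One arm receives a 12-week self-management package; the other receives a few administrative messages and the shared goal setting. A related count does not mean the same thing in both.
- **The label is unreliable whoever applies it.** A blinded judge does not know whether the participant received the package. An unblinded judge may apply the label more readily in one arm.

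The plausible harms, such as falls, are also common after stroke, so many could be called unrelated. At stake is whether the safety report could show an excess of such events in the intervention arm, or could show an imbalance that comes only from labelling.

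**Working it through.** The plan gives no harms figure to reproduce, so the check is mainly textual, followed by an illustration on assumed rates.

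**1. What the qualifier covers.** Grammatically, the relatedness phrase in the defining sentence could attach to the serious events alone. The last sentence of the section applies it to deaths, disability and life-threatening events. A rule that filtered the gravest events but not minor ones would be odd, so the restrictive reading of the whole definition is the more natural one.

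**2. Which harms are compared by arm elsewhere without a relatedness filter.**

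| Event or measure | Where | Relatedness filter |
|---|---|---|
| Emergency presentation for any cause, unplanned admission | Primary outcome; Table 2 | None |
| Recurrent stroke, cardiovascular event or death | Composite outcome; Table 2 | None |
| Number of hospital contacts | Table 3 | None |
| Anxiety and depression (HADS), disability (mRS) | Table 3 | None |
| Fall or other event treated outside hospital | Harms section only | Related only |

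The Framework section presents all outcome analyses as tests of effectiveness. The last row is the gap. Resource use might register a consultation, but its analysis is to be reported separately and would not identify the event as a harm. A fall that does reach hospital is merged with all other presentations.

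**3. Illustration (assumption only).** Current status of the trial gives 462 randomised; with 1:1 allocation that is 462 / 2 = 231 per arm. The event risks and the share *q* of events called related are assumed. Power stands in for how visible an excess would be; the plan specifies no such test. With n per arm, two-sided 5%, and p̄ the mean of p0 and p1:

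power = Φ{ [√n·(p1 − p0) − 1.96·√(2p̄(1 − p̄))] / √(p0(1 − p0) + p1(1 − p1)) }

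*All events, 20% vs 30%:* 231 × 0.20 = 46 and 231 × 0.30 = 69 participants. Power = Φ{(1.520 − 1.200) / 0.608} = Φ(0.525), about 70%.

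*Related events only, same q in both arms (a blinded judge), risks q × 20% and q × 30%:*

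| q | Expected, control vs intervention | Power |
|---|---|---|
| 0.05 | 2.3 vs 3.5 | 7% |
| 0.10 | 4.6 vs 6.9 | 10% |
| 0.20 | 9.2 vs 13.9 | 16% |
| 0.50 | 23.1 vs 34.7 | 37% |

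With 20% vs 25%, power is 25% for all events and 4% to 13% for related events over the same range of q. The normal approximation is rough at the smallest counts.

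*No true harm, 20% in both arms, label applied only in the intervention arm (an extreme unblinded judge):* 231 × 0.20 × q gives about 2, 5 or 9 related events against 0 for q = 0.05, 0.10 or 0.20. With true harm (30% in the intervention arm) and q = 0.05, the count is 231 × 0.30 × 0.05 = 3.5 against 0. A table showing about 2 vs 0 without harm and about 3 vs 0 with harm barely separates the two cases.

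**The case against.** The strongest reply is that the plan already compares the most serious events by arm whatever their cause. Death enters through the composite, and a fall leading to an emergency visit enters through the primary outcome. This stands. A reader might infer that the definition hides harms in general or leaves the safety data uninformative; the outcome tables do not support that.

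A reader might also infer that serious events never reach independent oversight unless someone has already called them related. The text does not say so. Reporting to the DSMC covers any severe event with no relatedness condition, and the monitor's adjudication of readmissions carries none either. What remains is an inconsistency: one sentence speaks of any *severe* events going to the DSMC and, if needed, the monitor, while the next limits the monitor's review to related *serious* events.

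Nor do the documents establish that the control count would be near zero. Controls share the goal setting and receive study messages, and if whoever assigns relatedness is blinded, attribution should be noisy rather than one-sided. The one-sided case above is an extreme, not a prediction.

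Finally, Supplemental Table III is not shown and may list more than the text implies. That is possible, but the text presents it as the format for safety as defined there, so the definition needs correcting whatever the table holds. Blinding limits bias in attribution; it does not make attribution accurate.

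**Conclusion.** The point holds in a limited form. The stated safety definition is restricted to related events, explicitly so for deaths and life-threatening events, and this is a worse basis for comparing harms than all reported events by arm. The identifiable loss is events that do not reach hospital and are not called related. For hospital presentations and for the composite that includes deaths, the comparison exists but is not tied to the safety report.

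The size cannot be taken from the documents. The illustration shows direction only: a filter that passes 5% to 50% of events can turn a fairly visible excess into a barely visible one, and one-sided labelling can create an imbalance from nothing. Both results rest on assumed risks and labelling shares. The conclusion also rests on the natural reading of the Harms section and on the fact that the plan does not say who assigns relatedness. This should be changed; it does not undermine the primary analysis.

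**What to change.** - **Harms section and Supplemental Table III.** Define safety as all reported adverse events, serious adverse events and deaths by randomised arm, irrespective of attribution. Give participants affected, event counts, and the risk difference with 95% CI. Keep relatedness as a descriptive column and state who assigns it and whether that person knows the allocation. Cross-refer to the primary outcome, hospital contacts, the composite, HADS and mRS as the all-cause comparisons already planned.
- **Statistical interim analyses and stopping guidance.** Reconcile the sentence on reporting any severe events with the sentence limiting the monitor's review to related serious events, and use one term consistently if severe and serious are meant to be the same.

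The cost is a wider table and a few sentences. The table can contain only what was recorded. The reporting duty to the DSMC implies that serious events are captured before relatedness is judged. For non-serious unrelated events the text is silent, so the sponsor should confirm whether they were collected; if not, the report should state that limit. The article anticipated data lock in the second quarter of 2024, so the definition could be changed before unblinding.

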### Statistical software

All analyses will be undertaken using Stata/SE 17.0 (StataCorp 2021).

## Current status of the trial

As of 20th of December 2023, 462 participants have been recruited and randomised. Recruitment to the trial was affected significantly by the COVID-19 pandemic and thereafter. Due to funding constraints, recruitment will conclude in December 2023. Data lock is anticipated for the second quarter of 2024, when all 90-day follow-up assessments should have been completed. Further details on analyses of longer-term outcomes to be determined through data linkage, including resource utilisation/costs within 12 months and composite (cardiovascular or death) outcomes, will be reported separately.

## Data Availability

The datasets used and/or analysed during the current study are available from the corresponding author on reasonable request.

## Abbreviations

EQ-5D-3L: The European Quality-of-Life questionnaire
GAS: Goal Attainment Scale
HADS: Hospital Anxiety and Depression Scale
heiQ: Health Education Impact Questionnaire
iVERVE: Inspiring Virtual Enabled Resources following Vascular Events
LUNS: Longer-term Unmet Needs Scale
mRS: Modified Rankin Scale
RCT: Randomised controlled trial
ReCAPS: Recovery-focused Community support to Avoid readmissions and improve Participation after Stroke
REDCap®: Research Electronic Data Capture
SMART criteria/goals: Specific, measurable, achievable, realistic and time-bound
SMART-GEM: SMART Goal Evaluation Method
SMS: Short message service
SSEQ: Stroke Self-Efficacy Questionnaire
